**Procedures**

A convenient sampling approach will be used, and a consecutive sample of pregnant women attending the selected prenatal clinic (located in Baharlou hospital) for receiving their routine prenatal care will be evaluated by their medical records for inclusion and exclusion criteria, by a colleague not involving in the study. Afterward, the objectives and goal of the study will be explained to eligible pregnant women, and after filing the consent form, they will be asked to complete the W-DEQ version A. women with a score of 38 and above (moderate and high FOC score) will be enrolled the study.

A randomized allocation into two groups of intervention and control with a 1: 1 ratio will be taken place during the routine prenatal visit in the hospital by a colleague who will be not involved in the study and computerized generated random sequences. In both intervention and control groups, the Tele-midwifery application will be installed on their smartphones during their prenatal visit. This application will only allow access to the questionnaires in the post-test, and follow-up stages for the participants in the control group. To prevent information contamination to the control group, after installing the application and before activating their account, women must select their group type as A or B. In addition, we will ask women in both groups to avoid sharing the contents of the application with each other for the duration of the trial. The Tele-midwifery application have two main stages for answering the questions. After filling the baseline questionnaire in the initial registration, including demographic, W-DEQ, and CBSE questionnaires, each group’s participants will complete the W-DEQ and CBSE questionnaires again at 34-36 weeks (after eight weeks of receiving the intervention). Participants will be also asked to inform the researcher by sending a message after hospitalization for their birth, whether in the Tele-midwifery application or by contacting the researcher directly by her phone number. Afterward, the W-DEQ version B questionnaire will appear in the application within the first two hours after birth, and the birth mode will be recorded. The investigators, care providers, data collectors, and statisticians will be masked from the allocation.

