**Continuous support and engagement of women:**

### To provide continuity of care between two prenatal visits and support participants in the intervention group, they can contact the researchers if they have concerns and questions about their pregnancy and birth care. The team of researchers including midwives and obstetricians will be available throughout the day (between 7 am to 9 pm), to provide women with an accessible source of information about their pregnancy and childbirth decisions. They can also write about their feelings and experiences publicly in the forum linked to the educational content, and pregnant women will have the opportunity to exchange their feelings with each other under the research team's supervision.

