**Project management**

SM, SK, and EB will participate in developing the tele-midwifery intervention. AK and SK will analyze the data, and AK, and SK will help interpret the results. EE, and SK will write the manuscript and EE, AK and SM will review it for critical intellectual content.

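### The four-role masking statement cannot hold for the investigators and care providers who deliver the app support, and is only weakly supported for data collectors and statisticians

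*Protocol*

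**What the plan says.** The Protocol, under Procedures, makes one masking statement: "The investigators, care providers, data collectors, and statisticians will be masked from the allocation". It lists four roles, with no exception for any member of the team. Participants are not on the list.

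The same section has a colleague outside the study carry out the 1:1 allocation and has each woman choose a group type, A or B, before her account is activated. For control women, "This application will only allow access to the questionnaires in the post-test, and follow-up stages for the participants in the control group". Participants, with no restriction to one arm, are asked to tell the researcher when they are hospitalized for birth, "whether in the Tele-midwifery application or by contacting the researcher directly by her phone number". The W-DEQ version B then appears in the app and birth mode is recorded. The person who records it is not named.

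Under Continuous support and engagement of women, the support is meant to "support participants in the intervention group, they can contact the researchers if they have concerns and questions about their pregnancy and birth care". As to who gives it, "The team of researchers including midwives and obstetricians will be available throughout the day", from 7 am to 9 pm. In the forum linked to the educational content, women can "exchange their feelings with each other under the research team's supervision".

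Under Project management, three team members "will participate in developing the tele-midwifery intervention" and two will analyze the data. One person is on both lists.

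**The concern.** A masking statement tells the reader which routes to bias have been closed. Here the people said to be masked include people who, by design, deliver the content of one arm. If the sentence passes unchanged into the trial report, readers will credit the trial with protection at four levels that it does not have in full.

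Three outcomes are affected in different ways. The W-DEQ (primary) and the CBSEI are completed by the women themselves, who can tell their arm from what the app shows them. Masking staff would protect these scores little, so the danger is mainly that the statement suggests more protection than exists. Birth mode is not a rating, but it follows from decisions in which staff take part. The Protocol says that the team's support is meant to inform women's decisions about pregnancy and childbirth. Knowledge of the arm, among anyone who also takes part in care, follow-up or recording, could therefore matter more for that outcome.

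**Working it through.** No figure is involved, so the check sets the sections side by side, role by role.

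**Investigators.** Procedures says masked. The support section has the researchers answering intervention women and supervising the forum. Control women have no such support and see only questionnaires. A team member who answers a support question, or reads a forum post, knows that the writer is in the intervention arm. Neutral A/B labels do not help, because it is the content that reveals the arm. Result: contradicted, for those who give the support.

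**Care providers.** The supporting team includes midwives and obstetricians, so the same reasoning applies to them. Routine prenatal care is given at the hospital clinic, and nothing says that clinic or labor-ward staff outside the team learn the allocation. Result: contradicted for the team's own clinicians, not for others.

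**Data collectors.** The scales are completed in the app in both arms, which needs no unmasked assessor. Against that, the hospitalization notice goes to the researcher before the W-DEQ version B is released and birth mode is recorded. The document does not say whether she belongs to the support team, who records birth mode, or from what source. Result: not contradicted, weakly supported.

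**Statisticians.** Of two analysts, one is also among the three developers and the other is not. Building an app is not the same as knowing which woman is in which arm, so the overlap weakens independence without proving unmasking. The document does not say who holds the key to A and B or whether the analysts receive coded data. Result: not contradicted, weakly supported.

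In sum, of the four roles named, one is contradicted for the members who give support, one is contradicted in part, and two stand without description.

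**The case against.** The strongest reply is that the defect is narrow.

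- Messaging as such is not confined to one arm, since all participants may send the hospitalization notice. This is correct. Only the question-and-answer support and the forum are confined to the intervention arm, and the point rests on those.
- Contact is optional. Women can write to the team but need not. This also stands. The 35 intervention women planned are an upper limit on those whose arm becomes known in this way, not a count.
- Allocation by an outside colleague and A/B labels are compatible with a masked analysis, and how analysts are kept masked is often left to an analysis plan. This is correct, and it is why the statistician role is called weakly supported and not false.
- The sentence never claims that participants are masked, so their knowledge of their arm does not contradict it. This is correct. That knowledge bears on how the self-reported results should be described, not on whether the sentence is true.

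A reader might go further and infer that no masking exists at all, that the developer-analyst must know the allocations, or that birth mode is recorded by people who know the arm. The Protocol supports none of these. It names no recorder, does not rule out the delivery record, does not say that the researcher who takes the hospitalization notice also gives support, and describes no access of the analysts to individual allocations.

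None of this rescues the sentence for the midwives, obstetricians and other researchers who give the support.

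**Conclusion.** The point holds in its narrow form. The masking statement is wrong as written for investigators and care providers who answer intervention women or supervise the forum. For data collectors and statisticians it may be true, but the Protocol gives little ground for it.

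The size of any bias cannot be derived from the document: it would depend on how many of the 35 intervention women use the support, and on whether those who give it also take part in care at birth, follow-up or recording, which is not stated. The conclusion rests on one assumption, that a person who answers a support message or reads the forum can see that the writer has access to it. Given that control women are limited to the questionnaires, this is hard to avoid.

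The sentence should be corrected, because it states a protection against bias that the design itself removes in part.

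**What to change.** Replace the sentence under Procedures with text to this effect:

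> Participants and the research-team members who deliver the app support are not masked. Routine clinic and labor-ward staff outside the research team are not told the allocation. The analyst works on a dataset with coded groups (A/B); the key is held until the analysis is complete by the colleague, not otherwise involved in the study, who carries out the randomization.

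Three further changes go with it:

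- Under Project management, give the analysis to the analyst who is not listed as a developer. The letters in the analysis file should be assigned independently of those chosen in the app, because a developer may know which letter opens the full content.
- State that birth mode is taken from the delivery record in the same way in both arms.
- Report the W-DEQ and CBSEI results as self-reported, open-label outcomes, and name this as a limitation.

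The cost is a less favourable masking statement and one task reassigned within the existing team. No extra staff, participants or visits are needed, and the planned tests are unchanged.

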**Dimensions of intervention:**

**Education**

The educational content of the Tele-midwifery application will be designed to include all possible causes of FOC in Iranian women, such as fear of labor pain, lack of information related to the mother and baby's health, what women should expect during labor and birth, the characteristics of each stage of labor, misconceptions such as distrust of healthcare providers, and complications of vaginal birth (16, 17). The educational content will be included information and exercises to increase women’s knowledge and challenge their underlying beliefs causing the FOC. Besides the educational information will be in form of text, audio, video, and image.

**Continuous support and engagement of women:**

### To provide continuity of care between two prenatal visits and support participants in the intervention group, they can contact the researchers if they have concerns and questions about their pregnancy and birth care. The team of researchers including midwives and obstetricians will be available throughout the day (between 7 am to 9 pm), to provide women with an accessible source of information about their pregnancy and childbirth decisions. They can also write about their feelings and experiences publicly in the forum linked to the educational content, and pregnant women will have the opportunity to exchange their feelings with each other under the research team's supervision.

### The control group will receive routine prenatal care. Currently, there is no specific guidelines in Iran, for providing care to pregnant women suffering from FOC. Routine prenatal care includes regular visits to monitor women and fetal health. To better access women in the control group, we will ask them not to uninstall the application from their mobile phones until birth and answer questionnaires after eight weeks and after childbirth.

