**Research protocol**

**Project summary**

Fear of childbirth (FOC) is a risk factor for maternal and child adverse outcomes and needs to be addressed during pregnancy. In this study, we aim to determine the effect of an mHealth application based on continuous support and education on FOC, self-efficacy, and birth mode in primiparous women. This study will be a single-center, Randomized Controlled Trial (RCT). It will conduct on seventy primiparous pregnant women with FOC attending a university-dependent governmental hospital in Tehran, Iran. Women who meet the inclusion criteria will randomly assign to two parallel intervention and control groups. Study participants in the intervention group will receive an mHealth application named Tele-midwifery, an interactive application based on multipurpose approaches, such as education and consultation, emphasizing continuous care for eight weeks. Women in the control group will receive routine prenatal care. FOC and self-efficacy will be measured via Wijma Delivery Expectancy/Experience (W-DEQ) questionnaire and Childbirth Self-efficacy Inventory (CBSEI), respectively. Data will be collected at the beginning of the study, 36 weeks of pregnancy, and after childbirth. Data will be analyzed by SPSS-25 using Chi-square, Fisher’s exact test, independent t-tests, and repeated-measures analysis of variance. We hypnotize that the intervention in this study will improve the FOC score, increase self-efficacy, and lower the number of C-sections.

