### Data management and statistical analysis

The data will be analyzed using SPSS software version 25, and p-value > 0.05 will consider a statistically significant level. First, the Kolmogorov‐Smirnov test will use to examine the normal distribution of data. After determining the normal distribution of data, to compare statistical differences of demographic data in two groups, an independent t-test, Chi-square test, and Fisher's exact test will be used. Also, for analyzing outcome variables, **r**epeated-measures analysis of variance (ANOVA) with a pairwise comparison of groups with Bonferroni correction, independent t-test, and Chi-square will determine the differences between the groups. **Sample size**

The sample size was calculated based on the results of Gözde Birsbir et al. (2016) study (18). A sample size of 70 pregnant women (35 in each group) was estimated. A two-sided t-test of difference between means with the power of 90%, the type one error equal to 0.05, mean difference of 21 between groups, and standard deviation of 7.2 was consider calculating the sample size. We accounted 20% attrition rate in estimating the sample size.

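### The app is both the treatment and the only stated route for the questionnaires, and only control women are asked to keep it, so loss of fear and self-efficacy scores could depend on treatment use in one arm

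*Protocol*

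**What the plan says.** The Project summary makes the app the treatment: "Study participants in the intervention group will receive an mHealth application named Tele-midwifery". Education and Continuous support and engagement of women describe its content, the forum and the access to the research team.

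Procedures also makes the app the means of data collection in both arms. "In both intervention and control groups, the Tele-midwifery application will be installed on their smartphones during their prenatal visit", and for controls its function is limited: "This application will only allow access to the questionnaires in the post-test, and follow-up stages for the participants in the control group". It goes on: "The Tele-midwifery application have two main stages for answering the questions". After the baseline forms, "participants will complete the W-DEQ and CBSE questionnaires again at 34-36 weeks". W-DEQ B is also presented in the app, shortly after birth. A telephone alternative is given only for telling the researcher about admission for birth. No paper, clinic, telephone or web route is stated for W-DEQ A, CBSEI or W-DEQ B.

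The paragraph on the control group, which follows Continuous support and engagement of women, contains the retention request: "To better access women in the control group, we will ask them not to uninstall the application from their mobile phones until birth". It also asks these women to answer the later questionnaires. No matching request is stated for the intervention arm.

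Under Sample size the protocol says "We accounted 20% attrition rate in estimating the sample size", without a split by arm or by cause. Outcomes names change in the FOC score as primary and change in self-efficacy as a secondary outcome.

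**The concern.** Removing the app has different consequences in the two arms. A control woman who deletes it loses a questionnaire holder. An intervention woman who deletes it ends her treatment and, as the protocol is written, also leaves the only stated route for her outcome scores. If women who find the app unhelpful are the ones who delete or abandon it, the scores that remain in that arm come mainly from users. The comparison would then drift from the effect of being offered the app towards the effect in women who kept using it.

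The primary outcome and self-efficacy are affected, as is the postpartum fear score. Birth mode is less exposed, because admission for birth can also be reported by telephone.

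The protocol itself fixes how outcomes are collected. An analysis plan may choose how to handle missing scores, but it cannot recover scores that were never collected. The named analysis adds to the concern: repeated-measures ANOVA as usually run in SPSS drops women with an incomplete series.

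**Working it through.** **Inputs from the protocol (Sample size).** 35 women per arm; 20% attrition; planned between-group difference of 21; SD of 7.2.

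**The plan's own figures.** 35 × 0.20 = 7 women lost per arm, if attrition is equal, leaving 28. The stated inputs do not reproduce the total of 70: 2 × (1.960 + 1.282)² × (7.2/21)² = 2.47, so 3 per arm, and 3/0.8 = 3.75, so 4 per arm or 8 in total. That is a separate matter. It affects the point below only in that 21 is a planning figure and not an estimate.

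**Assumptions that the protocol does not give.**
- D = 21: benefit in women who keep using the app.
- q: share of intervention women who stop and whose scores are lost.
- f: fraction of D that stoppers keep.
- s: untreated fear of stoppers minus that of users. If the analysis is of change from baseline, s is the difference in untreated change.
- Control loss is unrelated to fear.

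**Formulas.** Set the users' untreated mean to 0.
- Control mean: q·s.
- Intervention mean, all randomised: (1−q)(−D) + q(s − f·D).
- Effect in all randomised women: (1−q)D + q·f·D.
- Effect seen when stoppers are missing: D + q·s.
- Bias = seen − true = q[(1−f)D + s].

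**Results with s = 0** (the effect seen is always 21):

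| q | f | True effect | Overstatement |
|---|---|---|---|
| 10% | 0 | 0.9 × 21 = 18.9 | 2.1 (2.1/18.9 = 11%) |
| 20% | 0 | 0.8 × 21 = 16.8 | 4.2 (4.2/16.8 = 25%) |
| 20% | 0.5 | 16.8 + 0.2 × 10.5 = 18.9 | 2.1 (11%) |
| 20% | 1 | 21 | 0 |
| 30% | 0 | 0.7 × 21 = 14.7 | 6.3 (6.3/14.7 = 43%) |

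With s = 0 and f = 0, the relative overstatement is q/(1−q), so the 11%, 25% and 43% do not depend on the value of 21.

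**Sign.** The bias reverses when s < −(1−f) × 21. For example, with q = 20%, f = 1 and s = −5 the bias is 0.2 × (0 − 5) = −1.0: a true 21 would be seen as 20. With f = 0.5, stoppers would have to be more than 10.5 points less fearful than users for the sign to change.

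**With collection independent of the app.** If scores are obtained from all women whatever their app use, no stopper is missing and this bias is zero.

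**The case against.** A reader might infer that an intervention woman who stops treatment necessarily leaves the outcome data, and that the effect is therefore overstated, by 25%. The documents support neither step. A woman can ignore the content and still answer the questionnaires in the app. Nothing in the protocol withdraws non-users or bars contacting them. The 25% comes from one scenario: the whole attrition allowance is assigned to stoppers with no benefit and with otherwise similar fear. Other values that cannot be excluded give zero or the opposite sign.

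The retention request can also be read the other way. Control women hold an app that offers them only questionnaires, so they have the most reason to delete it. Asking them to keep it may make retention more equal. The paragraph describes the control arm alone, so its silence about the other arm is weak evidence that intervention women are not asked. Control women who delete the app may also be self-selected, so loss in that arm need not be unrelated to fear.

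These objections limit how certain and how large the bias can be said to be. They leave three facts in place: no other route for the questionnaires is written, that single route is the treatment in one arm only, and the retention request is stated for the other arm only.

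There is also a fair objection to the remedy. A fallback may be used more in one arm, so that mode of completion differs by arm, and completion at the clinic could add staff contact in a trial that declares care providers and data collectors masked. Self-completion answers most of the second point; the first remains as a cost.

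**Conclusion.** The point holds as a design weakness with a possible bias. Loss of the primary outcome and of self-efficacy scores could depend on treatment use in the intervention arm only. Overstatement is the most plausible direction, because it follows if stoppers benefit less and are missing, but it is not established.

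At 20% intervention loss the illustration runs from zero to 4.2 points (25%), with 2.1 points (11%) if stoppers keep half the benefit. It rests on a 21-point benefit in users, control loss unrelated to fear, and similar untreated fear in stoppers and users. If stoppers are sufficiently less fearful women, the sign reverses. None of these figures is an estimate for this trial. The change is worth making because it is cheap and must be made before data are collected.

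**What to change.** In Procedures, state that stopping or uninstalling the app is not withdrawal from follow-up. State also that any woman in either arm who has not completed a due questionnaire in the app self-completes the same form by another route:
- W-DEQ A and CBSEI: through a link outside the app, or on paper at a routine prenatal visit.
- W-DEQ B: through the same kind of link, or on paper in hospital after birth.

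Record the mode of completion for every questionnaire.

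In the control-group paragraph, replace the one-sided request with one worded identically for both arms: keep the app or otherwise stay reachable, and answer the questionnaires.

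The cost is a wording change, a link and printed copies of existing questionnaires, used at contacts that women already have. The downside is that a few scores are completed in a different mode, possibly unevenly by arm.
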